### Follow-up protocol

During the study period, study visits are scheduled at week -2 (high-dose group only), and 1, 3, 6, 9, 12 months. At each visit, patients undergo a complete physical examination, medical history-taking, and assessment of drug compliance. Investigators evaluate all clinical and laboratory adverse events at each visit. To monitor safety, serum creatinine and urea nitrogen concentrations are determined at every study visit. New York Heart Association (NYHA) functional class [26] and predefined clinical events are recorded at each clinical visit. Echocardiographic examination and neurohormonal assay are performed at 3 and 12 months after discharge. After a routine review with 50% of the patients enrolled, early cessation of the trial will be decided by the institutional review board and study sponsor when the trial appears to be futility or causing unexpected harm to participants.

### Adverse effects

Analysis of safety related data is performed with respect to frequency of serious adverse events, stratified by causality and intensity of morbidity in both treatment groups.

Patients are interviewed at each visit about the occurrence of any adverse events, including the time of onset, duration, and severity; all information is recorded on a case report from. The causal relation to the study drug and the intensity of adverse events are evaluated by the investigators. Serious adverse events (SAE) have to be reported to the institutional review board and study sponsor by the principal investigator within 24 hours after the SAE becomes known.

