**Method/Design:**

Valsartan in post-MI remodeling (VALID) is a randomized, open-label, single-blinded multicenter study designed to compare the efficacy of different clinical dose of valsartan on the post-MI ventricular remodeling. This study also aims to assess neurohormone change and clinical parameters of patients during the post-infarct period. A total of 1116 patients with left ventricular dysfunction following the first episode of acute ST-elevation MI are to be enrolled and randomized to a maximal tolerable dose (up to 320 mg/day) or usual dose (80 mg/day) of valsartan for 12 months in 2:1 ratio. Echocardiographic analysis for quantifying post-MI ventricular remodeling is to be conducted in central core laboratory. Clinical assessment and laboratory test are performed at fixed times.

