## Methods and Design

### Study design

VALID is a prospective, multicenter, randomized, open-label, active controlled study with two parallel study groups. VALID is being conducted in 18 tertiary hospitals throughout South Korea. Participants are randomly allocated into the usual dose group and high dose group and followed-up for 12 months after discharge. Overall study algorithm is depicted in Figure 1. Baseline echocardiographic examination and neurohormonal assay are performed before discharge. Study approval was given by the institutional review board at each participating center, and consecutive, eligible patients are provided written informed consent.

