### Intervention and comparator descriptions

Eligible patients are randomly assigned in a 1:2 fashion to either the usual dose group (valsartan 80 mg/day) or the high dose group (valsartan up to 320 mg/day). In the usual dose group, valsartan 40 mg twice a day is administrated throughout the study period. For those in the high dose group, dose is up-titrated to 80 mg twice a day before hospital discharge and finally to 160 mg twice a day after 2 weeks during outpatient visits. The process of the trial conduct is illustrated in Figure 2. If up-titration is not clinically feasible, either because of hypotension or deepening azotemia, the previous dose is administered subsequently as maximal tolerable dose.

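### The stated safety analysis covers serious adverse events, so non-serious hypotension and renal worsening, the harms named as limiting up-titration, have no stated between-arm comparison

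*Protocol article*

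**What the plan says.** Under Adverse effects, the protocol article states what the analysis of safety data is: the "frequency of serious adverse events, stratified by causality and intensity of morbidity in both treatment groups". The same section gives the attribution to the sites: "The causal relation to the study drug and the intensity of adverse events are evaluated by the investigators". Study design calls the trial a "prospective, multicenter, randomized, open-label, active controlled study with two parallel study groups". The abstract says "randomized, open-label, single-blinded multicenter study" without naming the blinded party, and no section describes blinded assessment of adverse events.

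Collection is wider than the stated analysis. Follow-up protocol says: "Investigators evaluate all clinical and laboratory adverse events at each visit". For renal safety it adds that "serum creatinine and urea nitrogen concentrations are determined at every study visit". Under Adverse effects: "Patients are interviewed at each visit about the occurrence of any adverse events, including the time of onset, duration, and severity".

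Intervention and comparator descriptions names the harms expected to limit the high dose. Up-titration may not be feasible "either because of hypotension or deepening azotemia", and the patient then stays on the dose already reached.

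**The concern.** The trial sets a maximal tolerable dose, up to 320 mg/day, against 80 mg/day, and its abstract promises information on optimal dosing. Its Discussion suggests that worry about intolerance may be one reason physicians keep patients on lower doses. Tolerability is therefore part of the trial's own rationale.

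The named tolerability problems are low blood pressure and worsening renal function. Many such episodes could be handled by holding the dose and never become serious events. That is an inference from the titration rule; the protocol gives no proportion. Any such episode falls outside the stated analysis. The report could then show similar serious-event rates in the two arms while a real excess of non-serious hypotension or creatinine rise sat unanalysed in the case report forms.

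**Working it through.** **Step 1. Set collection against analysis.**

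| Item | Collected? | Between-arm comparison stated? |
|---|---|---|
| Serious adverse events | Yes (Adverse effects) | Yes, by causality and intensity |
| Non-serious adverse events | Yes, with onset, duration and severity (Adverse effects; Follow-up protocol) | No |
| Hypotension | Through examination and adverse event interview; blood pressure is not named as a scheduled measurement | Only if serious, and not as a named item |
| Creatinine, urea nitrogen | Yes, every visit (Follow-up protocol) | No |
| Failed up-titration | Implied by the titration rule | No; arises in the high-dose arm only |
| Stopping study drug | Partly: compliance at each visit; withdrawals from the trial documented | No |

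The secondary outcomes (Outcomes measurement, Table 2) are NYHA class, death, hospitalization, revascularization, neurohormones and echocardiographic indices. Statistical analyses names methods for baseline data, the primary outcome, clinical events, neurohormones and echocardiography, and none for adverse events or renal function.

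**Step 2. What the serious-event table can and cannot show.** Stratifying does not exclude anything. For each arm, total serious events = sum over the causality strata, so the comparison regardless of attribution can be recovered. What the table cannot show is any event below the threshold of seriousness.

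**Step 3. Illustrate the size.** The protocol states no safety figure, so there is nothing to reproduce. Inputs: n1 = 372 usual dose and n2 = 744 high dose (Figure 1 legend), two-sided 5%. All event rates are assumptions.

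- Pooled rate: p̄ = (n1·p1 + n2·p2)/(n1 + n2)
- SE under the null: SE0 = √[p̄(1 − p̄)(1/n1 + 1/n2)]
- SE under the alternative: SE1 = √[p1(1 − p1)/n1 + p2(1 − p2)/n2]
- Power ≈ Φ[(p2 − p1 − 1.96·SE0)/SE1]

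| Assumed rates (usual v high) | p̄ | SE0 | SE1 | z | Power |
|---|---|---|---|---|---|
| 5% v 10% | 0.0833 | 0.01755 | 0.01577 | 0.99 | 84% |
| 1% v 2% | 0.0167 | 0.00813 | 0.00728 | −0.82 | 21% |
| 0.5% v 1% | 0.0083 | 0.00577 | 0.00517 | −1.22 | 11% |

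Other assumed pairs give 65% (10% v 15%) and 70% (2% v 5%). With only the 279 and 558 patients left after the planned 25% loss, 5% v 10% gives 71% and 1% v 2% gives 16%.

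The formula matters. Using SE1 in both places gives 89%, 28% and 16% for the three tabulated pairs. That version is optimistic here because the larger arm is given the higher rate. The contrast between common and rare events is the same under both.

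**Step 4. Ascertainment.** Follow-up protocol gives the high-dose arm one visit that the usual-dose arm does not have (printed as week -2). More visits mean more chances to record an event or a raised creatinine, so a raw comparison over all visits would be tilted against the high dose.

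**The case against.** The strongest objection is that this is a one-sentence summary in a journal article. It does not say that other data go unanalysed, and tables of non-serious events and laboratory changes are commonly left to a full protocol or analysis plan. This stands in part: the point concerns the analysis as stated, and a reader should not infer that the sponsor will never look at these data. But the article does more than stay silent. It says what the safety analysis is, and that is narrower than the data it collects and the harms it names.

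Three stronger readings are tempting and are not supported.

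- **That hypotension and azotemia are left out of the safety analysis altogether.** Episodes that meet the definition of serious enter the count. Hospitalization and all-cause death are also secondary outcomes, defined without regard to attribution, and a review at 50% enrolment looks for unexpected harm. The gap is non-serious events and laboratory change.
- **That the causality split undermines the serious-event comparison.** Investigators do judge causality in an open-label trial, so counts of drug-related events could be shifted by knowledge of the dose. The analysis is not restricted to related events, however, and the totals by arm are unaffected by how they are attributed.
- **That the power figures measure what the trial will lose.** They rest on assumed rates, and safety tables are usually descriptive. They show only why a comparison confined to rare events tells little.

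It is also fair to say that the primary hypothesis is about remodeling, and this point does not touch it.

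**Conclusion.** The point holds in limited form. As stated, the safety analysis has no between-arm comparison of non-serious hypotension or renal worsening, although the protocol names these as the harms that limit up-titration and collects renal values at every visit. The primary result is unaffected, but a conclusion about dose would lack much of its tolerability evidence.

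The size cannot be derived from the document. Under the assumed rates, a doubling is likely to be detected when events are common (about 84% power at 5% v 10%) and unlikely when they are rare (about 21% at 1% v 2%, about 11% at 0.5% v 1%).

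The conclusion assumes that a meaningful share of dose-limiting episodes is non-serious, and that no unseen document already adds the comparison. If an analysis plan does so, what remains is to bring the published statement into line with it.

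**What to change.** Amend the Adverse effects section so that, besides serious adverse events, the following are compared by randomised arm regardless of investigator attribution, each as a risk difference with 95% CI:

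1. all adverse events;
2. hypotension recorded as an adverse event;
3. worsening renal function from the scheduled creatinine values, under a definition fixed by the investigators before the data are compared;
4. discontinuation of study drug.

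Base these comparisons on the visits common to both arms, and list findings from the high-dose arm's extra visit separately so that nothing is hidden. Report total serious adverse events by arm and keep the causality split as description. Describe failed up-titration, with its reason, in the high-dose arm only, since the usual-dose arm has no step to fail.

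The cost is a few more safety tables. Dosing, visits and clinical rules stay as they are, and the data are already collected, except that the case report form should be checked for a field recording when and why study drug was stopped.

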### Withdrawals

Patients are free to withdraw trial participation at their own request at any time and without giving reasons for their decision. Moreover, the primary investigator can withdraw study patients, if continuation of the trial would be detrimental to the patient's

well being. Withdrawals will be documented in the case report form and in the patient's medical records and all ongoing severe adverse event have to be followed up.

### Sample size

The sample size calculation is based on the primary outcome and the primary analysis for the intention-to-treat population. In the VALIANT Echo study, [17] a sample size of 600 patients was determined necessary to detect, with a 90% power, a 7.6 mL difference in end-diastolic volume between the treatment groups. Because the present study enrolls more patients with mild degree (EF < 50%) LV dysfunction, we anticipate that the difference of ventricular volume between treatment groups will be smaller than the previous study. Thus, detection of 3.8 mL difference, with a two-sided level of significance α = 5% and a power of 1-β = 90%, in end-diastolic volume between treatment groups would require a sample size of 279 patients in a usual dose of valsartan group and 558 patients in a high dose valsartan group. Assuming 25% of patients are lost to follow-up or with missing data, as reported in the GISSI-3 study [27], the required sample size of this study will be a total of 1,116 patients. The study is likely to be underpowered in terms of assessing secondary outcomes if this size is employed. Variability data for the outcome measures could be used to inform design a subsequent larger-scale randomized controlled trial, if post hoc analysis reveals this study to be underpowered.

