However, the optimal level of RAAS antagonism in the treatment of heart failure or post-MI remodeling is still a matter of debate. Although administration of higher dose of angiotensin-converting enzyme (ACE) inhibitor was more beneficial than lower dose in animal model of post-MI remodeling [16], results of clinical studies were not confirmatory. In the VALIANT study [17], addition of ARB valsartan to ACE inhibitor resulted in similar degree of post-MI left ventricular (LV) remodeling compared to either drug alone, although in the Val-HeFT study [18], LV remodeling in heart failure was more favorable in the combination therapy group. In several clinical studies that directly compared different doses of ACE inhibitors in patients with chronic heart failure, the results of clinical outcomes as well as neurohormonal responses were inconsistent, and sometimes irrelevant because of the impractical dosing of drugs chosen for the comparison. In the ATLAS study [19], patients receiving high-dose lisinopril (32.5-35.0 mg/day) had a nonsignificant (8%) lower risk of death and a significant (12%) lower rate of death and hospitalization compared with patients receiving low-dose lisinopril (2.5-5.0 mg/day). The CHIPS trial [20] compared low-dose (50 mg/day) with high-dose (100 mg/day) captopril therapy and demonstrated a nonsignificant trend toward less worsening heart failure and hospitalization in the high-dose group. In the NETWORK trial [21], there was no difference in the primary endpoint of combined death, heart failure-related hospitalization, and worsening of heart failure among the three groups of low dose (5 mg/day), medium dose (10 mg/day), and high dose (20 mg/day) enalapril therapy. Furthermore, the lower dose used in NETWORK (enalapril 5 mg/day) [21] was too small, and the higher dose used in ATLAS (lisinopril 35 mg/day) [19] was excessive for practical use. The recent publication of the Heart failure Endpoint evaluation of Angiotensin Antagonist Losartan trial (HEAAL) presented notable evidence of the superiority of 150 mg/day of losartan versus 50 mg per day on the primary outcomes of death or hospitalization in patients with systolic heart failure [22]. However, the study subjects were limited to patients who were intolerant to ACE inhibitors [22], precluding extrapolation of the result to general patients. Furthermore, the optimal dosing of ARB agents has not been explored in the population of post-MI. Thus, the question of whether submaximal dose of ARB, which are lower than those in major pivotal trials but typically used in clinical practice, can offer similar benefit in post-MI ventricular remodeling remains to be solved. This is more so in the Asian population, wherein moderate dose ARB has been shown to provide sufficient protection from cardiovascular risk [23]. Therefore, the primary objective of the VALsartan in post-mI remoDeling (VALID) study is to address this issue in Korean patients who suffered their first acute ST-elevation MI by comparing the impact of different doses of valsartan, an ARB demonstrated as effective as ACE inhibitor in post-MI patients [12], on echocardiographic variables of left ventricular remodeling during the follow-up period of 1 year. The comparison dose of valsartan will be 80 mg per day, as commonly prescribed after MI in Korea, versus 320 mg per day, a targeted dose in major clinical trials [12,24].

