### Randomization

Randomization will take place following initial echocardiographic estimation of left ventricular ejection fraction, which is conducted after stabilization by reperfusion therapy or conservative treatment. Eligible patients are randomly assigned in a 1:2 ratio to receive the usual dose (valsartan 80 mg/day) or a high dose (valsartan up to 320 mg/day). Random allocation with stratified technique is generated automatically by a centralized web based tool (http://www.cnrres.co.kr/valid) so it cannot be influenced by researchers.

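### The 279 + 558 patients said to give 90% power for 3.8 mL do not follow from the VALIANT Echo figures that are their only cited basis

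*Protocol article*

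**What the plan says.** The Sample size section gives one quantitative basis. In VALIANT Echo, "a sample size of 600 patients was determined necessary to detect, with a 90% power, a 7.6 mL difference in end-diastolic volume" between treatment groups. Because VALID enrols patients with milder left ventricular dysfunction, "we anticipate that the difference of ventricular volume between treatment groups will be smaller than the previous study". From this the section concludes that a 3.8 mL difference in end-diastolic volume, at a two-sided 5% level and 90% power, "would require a sample size of 279 patients in a usual dose of valsartan group and 558 patients in a high dose valsartan group". That is 837 evaluable patients. "Assuming 25% of patients are lost to follow-up or with missing data", the total becomes 1,116.

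The Randomization section fixes the allocation: "Eligible patients are randomly assigned in a 1:2 ratio to receive the usual dose (valsartan 80 mg/day) or a high dose". The Background indicates that VALIANT had three arms: "addition of ARB valsartan to ACE inhibitor resulted in similar degree of post-MI left ventricular (LV) remodeling compared to either drug alone". The Sample size section does not say how the 600 were divided.

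**The concern.** The section presents 279 + 558 as a consequence of the VALIANT Echo calculation. For a fixed SD, alpha and power, the number needed varies with the inverse square of the difference, so halving the difference quadruples it. Moving from 1:1 to 2:1 allocation adds a further 12.5% to the two-group total. One comparison in VALIANT Echo used 400 patients (two of three arms) or 600 (two arms). The plan goes only to 837, where the same SD would call for 1,800 or 2,700.

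At stake is the power claim for the primary outcome. The section warns of low power only for secondary outcomes, so a reader takes the primary comparison to be secure. If the SD is nearer to what the cited source implies, a real 3.8 mL effect could be missed far more often than the 10% of the time that 90% power implies. The Follow-up protocol section also allows early stopping for futility after a review at 50% enrolment. That judgement is harder to make well if the design power is overstated.

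**Working it through.** **Inputs from the Sample size and Randomization sections.** VALIANT Echo: 600 patients, 7.6 mL, 90% power. VALID: 3.8 mL, two-sided 5%, 90% power, 279 usual dose and 558 high dose, 25% loss.

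**Assumptions, not in the article.** Two or three equal arms in VALIANT Echo, two-sided 5% there, and all 600 evaluable. These are varied in step 6.

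Constants: z(0.975) + z(0.90) = 1.960 + 1.282 = 3.2415, and √(1/279 + 1/558) = 0.07332.

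**1. Loss to follow-up.** 279/0.75 = 372, 558/0.75 = 744, 837/0.75 = 1,116. This step is correct.

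**2. SD needed for the plan's own figure.** SD = 3.8 / (3.2415 × 0.07332) = 15.99 mL. With that SD, n(usual) = 1.5 × (3.2415 × 15.99/3.8)² = 279, so the plan's number is reproduced only at about 16.0 mL.

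**3. SD implied by the cited source.** SD = 7.6 × √(n per arm/2) / 3.2415.
- Three arms of 200: 7.6 × 10/3.2415 = 23.4 mL.
- Two arms of 300: 7.6 × 12.25/3.2415 = 28.7 mL.

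Cross-check: at 15.99 mL, detecting 7.6 mL with 90% power would have needed 2 × (3.2415 × 15.99/7.6)² = 93 per arm, not 200 or 300.

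**4. Power for 3.8 mL with 279 + 558.** Power = Φ(3.8/(SD × 0.07332) − 1.960).
- SD 23.4: Φ(2.210 − 1.960) = 0.599.
- SD 28.7: Φ(1.805 − 1.960) = 0.438.

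**5. What 90% power would mean at those SDs.** Detectable difference = 3.2415 × SD × 0.07332 = 5.57 or 6.83 mL. Holding 3.8 mL instead, the evaluable total is 3 × 1.5 × (3.2415 × SD/3.8)² = 1,800 or 2,700.

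**6. Other readings of the 600.** With 25% loss inside the 600, 450 remain (150 or 225 per arm). With a multiplicity-adjusted alpha in VALIANT Echo, 3.2415 in step 3 becomes 3.5230 (alpha 0.025) or 3.6755 (alpha 0.05/3). VALID stays at two-sided 5%.

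| Reading of the 600 | Evaluable per arm | SD (mL) | Power for 3.8 mL | Difference at 90% power (mL) |
|---|---|---|---|---|
| Three arms, no loss | 200 | 23.4 | 60% | 5.6 |
| Two arms, no loss | 300 | 28.7 | 44% | 6.8 |
| Three arms, 25% loss | 150 | 20.3 | 72% | 4.8 |
| Two arms, 25% loss | 225 | 24.9 | 55% | 5.9 |
| Three arms, 25% loss, alpha 0.025 | 150 | 18.7 | 79% | 4.4 |
| Three arms, 25% loss, alpha 0.05/3 | 150 | 17.9 | 82% | 4.3 |

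The last row is Φ(2.894 − 1.960) = 0.8249. None of these readings gives 90%.

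**The case against.** The strongest reply is that the true SD is unknown, so the plan may be sound. This is a journal article, and the full protocol may hold an SD of about 16 mL. That is possible, and a missing SD alone would be no finding. What stands is that the article prints a derivation whose premise and conclusion disagree.

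A related reply is that the SD implied by VALIANT Echo may not be VALID's SD. The Outcomes measurement section names the change in left ventricular volume index, while the sample size is in mL of end-diastolic volume. Milder patients may also vary less. Both points are fair. They are reasons to state the SD and its scale, and they rule out treating any one power figure above as the answer.

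A third reply is covariate adjustment. The Statistical analyses section plans an analysis of covariance. To bring 23.4 or 28.7 mL down to 16.0 mL, covariates would have to explain 1 − (16.0/23.4)² = 53% or 1 − (16.0/28.7)² = 69% of the variance. The covariates named are age, gender and cardiovascular risk factors; baseline volume is not among them. The same section also plans two-sample t tests for the primary outcome.

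A reader might infer from the table that no assumption can reach 90%. That is too absolute. From the last row's 17.9 mL, covariates explaining about 20% of the variance (1 − (16.0/17.9)² = 0.20) would suffice. That stacks several conditions the article does not state, but it cannot be excluded.

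**Conclusion.** The stated sample size does not follow from its only cited basis. It needs an SD of about 16.0 mL, against 23.4 mL (three arms) or 28.7 mL (two arms) from the cited figures, and nothing in the text argues for the lower value. On those SDs, power for 3.8 mL is about 60% or 44% rather than 90%. With 25% loss inside the 600 it is 72% or 55%. Adding a multiplicity-adjusted alpha to the three-arm case gives 79% to 82%. All of this rests on equal arms, the normal approximation, and the VALIANT Echo SD carrying over to VALID.

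Three stronger readings are not supported. First, the documents do not show that VALID's power is 44% to 60%; the power is unknown until an SD is given. Second, a reader might take the words "if post hoc analysis reveals this study to be underpowered" as a plan to explain away a null result. The sentence is about using variability data to inform a later, larger trial, and it follows a remark on secondary outcomes. Third, a reader might infer that a non-significant result will be reported as equivalence of the doses. The Trial objectives and Statistical analyses sections set out a test for a difference and plan no claim of similarity, so 3.8 mL should not be turned into a similarity margin.

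**What to change.** Keep 1,116 patients and correct the statement.

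1. State the SD used for 279 + 558, its source and its scale: volume or volume index, and change from baseline or final value.
2. If an SD of about 16 mL can be justified, give that justification; the stated 90% then stands. If not, restate the power for 3.8 mL and the difference detectable with 90% power, using the SD the cited source supports. Show the assumed arms, alpha and attrition of VALIANT Echo beside the result.
3. At the review already planned at 50% enrolment, compare the assumed SD with the SD of both arms combined. This does not require a comparison of the arms.

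The cost is wording and one summary figure at an existing review. No patients are added. The stated power will probably become less favourable.

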### Statistical analyses

A consultant group of statisticians has been appointed to conduct the statistical work for this study, including data completion, interim analysis, application of statistical technique and final assessment. The principal analysis will be an intention-to-treatment basis. For baseline characteristics, continuous variables are assessed using the Student *t *test and discrete variables are compared using the chi-square test. The two-sided null-hypothesis for the primary outcome measure states that usual and high dose valsartan lead to the same expected change of ventricular remodeling during the 12 months after MI. This null-hypothesis will be tested by application of an analysis of covariance that adjusts for age, gender, and cardiovascular risk factors. Primary outcome will be compared using 2-sample *t *tests. Event-free cumulative survival rates are plotted using the Kaplan-Meier method and comparisons are made between patients with and those without clinical events using the log-rank test. A Cox proportional hazards model with the use of forward selection based on the likelihood ratio test will be implemented for multivariate analysis to determine which prognostic factors identified in the univariate analysis were significantly related to 12-month clinical events. Assessments for the change of neurohormone and other echocardiographic indices will be compared between treatment groups at 12-month follow-up using 2-sample *t *tests.

We will compare proportions of missing data using chi-square tests and agreement between data collection methods using Lin's Concordance Correlation Coefficient. Additionally, sensitivity analyses will be conducted using different patient populations (per protocol population excluding patients with relevant protocol violations), different imputation techniques for missing values, and different statistical methods for taking into account covariates. A value of p < 0.05 will be considered statistically significant.

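### The named primary tests cannot by themselves include the 25% of patients expected to lack follow-up data, and the scheduled 3-month echo has no stated role in the primary analysis

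*Protocol article*

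**What the plan says.** All references are to the protocol article.

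- **Statistical analyses, population:** "The principal analysis will be an intention-to-treatment basis". The Sample size section also ties its calculation to the intention-to-treat population.
- **Sample size:** the target is "detection of 3.8 mL difference" in end-diastolic volume, "with a two-sided level of significance α = 5% and a power of 1-β = 90"%, which "would require a sample size of 279 patients in a usual dose of valsartan group and 558 patients in a high dose valsartan group". The total is then raised to 1,116: "Assuming 25% of patients are lost to follow-up or with missing data".
- **Statistical analyses, tests:** the primary null hypothesis is tested by an analysis of covariance with demographic and risk-factor covariates. The same section also assigns the primary outcome to two-sample t tests.
- **Statistical analyses, missing data:** the proportions missing are compared by chi-square. The sensitivity analyses include a per-protocol set and "different imputation techniques for missing values".
- **Follow-up protocol:** "Echocardiographic examination and neurohormonal assay are performed at 3 and 12 months after discharge". The baseline echo is done before discharge (Study design). No analysis is described that uses the 3-month volumes for the primary comparison.

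**The concern.** An analysis of covariance or a t test on 12-month change needs a 12-month value for every patient it includes. The plan expects a quarter of patients to lack follow-up data, names only these tests, and places imputation outside the primary analysis. Read together, the primary comparison is most naturally one of patients with a 12-month echo, under an intention-to-treat label.

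That matters if the patients without a 12-month echo remodel differently and the difference is not the same in the two dose groups. The article makes this plausible without establishing it:

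- The trial is open-label.
- Hypotension and worsening renal function limit titration in one arm only.
- That arm has an extra visit at 2 weeks.
- Investigators may withdraw patients.
- The Background links dilation to heart failure and poor prognosis.

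Many patients lost after month 3 will already have a 3-month volume. It carries information about their 12-month volume, and the named tests leave it unused.

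**Working it through.** **1. The plan's own figure.** Evaluable patients: 279 + 558 = 837. Inflation: 837/(1 − 0.25) = 1,116; by arm 279/0.75 = 372 and 558/0.75 = 744. The stated total reproduces exactly. The difference, 1,116 − 837 = 279 (93 usual dose, 186 high dose), is credited with no primary-outcome information.

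**2. An SD to work with.** None is stated. Solving the two-means formula for the SD, with 1.960 + 1.282 = 3.242:

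SD = 3.8 / [3.242 × √(1/279 + 1/558)] ≈ 16.0 mL.

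This is an implied value. I use 16 mL and, as an assumed upper value, 25 mL. Everything is in mL of volume, as in the Sample size section, although the primary outcome is an index.

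**3. Bias of a completers' comparison.** Assumptions: 25% missing at 12 months in each arm; correlation r = 0.7 between 3- and 12-month change; log-odds of being missing linear in standardised 3-month dilation, with a slope that may differ by arm. With the intercept set to give 25% missing, the mean standardised 3-month dilation among patients still observed is:

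| Slope | Mean among observed |
|---|---|
| 0.20 | −0.0496 |
| 0.25 | −0.0618 |
| 0.30 | −0.0738 |
| 0.50 | −0.1195 |

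Shift in the dose contrast = r × SD × (difference between arms in that mean).

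| Slopes, usual vs high | SD 16 mL | SD 25 mL |
|---|---|---|
| 0.30 vs 0.20 | 0.7 × 16 × 0.0242 = 0.27 mL | 0.7 × 25 × 0.0242 = 0.42 mL |
| 0.50 vs 0.25 | 0.7 × 16 × 0.0577 = 0.65 mL | 0.7 × 25 × 0.0577 = 1.01 mL |
| equal in both arms | 0 | 0 |

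With the steeper slope in the usual-dose arm, a true 3.8 mL is estimated as 3.8 − 0.65 = 3.15 mL (SD 16) or 3.8 − 1.01 = 2.79 mL (SD 25). With the slopes swapped it becomes 4.45 or 4.81 mL. The shift is therefore about 0.3 to 1.0 mL, or 7% (0.27/3.8) to 27% (1.01/3.8) of the target, in either direction.

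The zero row needs equal loss rates as well as equal slopes. If the same 279 losses fell as 30% of 372 and 22.5% of 744, and missing patients dilated 5 to 10 mL more than observed ones in both arms, the shift would be (0.30 − 0.225) × 5 to 10 = 0.4 to 0.75 mL.

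**4. What a model with the 3-month echo recovers.** In 2,000 simulated trials (372 vs 744, SD 25 mL, slopes 0.5 vs 0.25, truth 3.8 mL), the mean completers' estimate was 2.75 mL and the mean estimate using the 3-month echo was 3.84 mL. Missingness there depends only on the 3-month value, which is the case most favourable to the model.

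**5. Precision.** With 75% observed at 12 months and a fraction n3 observed at 3 months (assumed), the variance relative to completers is (1 − r²) + r² × 0.75/n3:

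- r = 0.6, n3 = 0.85: 0.64 + 0.318 = 0.958
- r = 0.7, n3 = 0.875: 0.51 + 0.42 = 0.930
- r = 0.8, n3 = 0.875: 0.36 + 0.549 = 0.909

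The reduction is about 4 to 9%. At the implied SD of 16 mL, power moves from 90% to about 90–94%, over r from 0.3 to 0.8 and 25–100% of the missing patients having a 3-month echo.

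**The case against.** A reader might infer that the plan discards a quarter of its patients, deaths included, and so is not intention-to-treat. The article does not support that.

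- It nowhere says that patients without a 12-month echo are excluded.
- Inflating for attrition is a power allowance and does not define the analysis set; an imputed or likelihood-based analysis could be sized the same way.
- The word used for imputation in the sensitivity analyses leaves open that the primary analysis also imputes.
- The 25% is described as loss or missing data. Deaths are not mentioned there and no death rate is given.
- Missing-data detail is commonly left to a fuller document, so its absence alone is no finding.

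A reader might also infer a bias as large as the target effect. With 25% missing per arm, that would need the gap between missing and observed patients to differ between arms by 3.8/0.25 = 15.2 mL, nearly one implied SD. Nothing in the article points to that. The differential slopes, and their direction, are assumptions.

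These points limit the concern without removing it. The article does more than stay silent: it names the tests, states the expected loss, and places imputation among the sensitivity analyses. The chi-square comparison of missingness would detect unequal loss rates, but not unequal dependence on dilation at equal rates, which is the mechanism behind the main shift calculated here.

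**Conclusion.** The point holds as a weakness in the stated choice of primary method. The named tests do not handle a missing 12-month volume, the plan expects 25% of patients to have missing data or be lost, and a scheduled 3-month measurement is given no part in the primary comparison. That completers are the primary set is the natural reading, not stated text.

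The possible bias is about 0.3 to 1.0 mL against 3.8 mL, in either direction. It rests on SD 16–25 mL, r = 0.7, 25% loss per arm, and log-odds slopes from 0.3 vs 0.2 to 0.5 vs 0.25, none of which the article gives except the 25% overall. With equal dependence and equal loss there is essentially no bias. The precision gain is modest, so possible bias is the main reason to change. The change is worth making because it is cheap; there is no evidence that the result would be badly wrong without it.

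**What to change.** - **Primary analysis:** a repeated-measures (constrained longitudinal) model of volume index at baseline, 3 and 12 months in all randomised patients, with treatment-by-visit terms and the 12-month dose contrast as the primary estimate. Constraining the baseline means to be equal presumes that the baseline echo precedes any effect of the allocated dose; otherwise enter baseline as a covariate with a baseline-by-visit term.
- **Sensitivity:** keep the analysis of covariance and t test on patients with a 12-month echo. Among the imputation analyses already planned, include a delta-adjusted one, and add one that ranks deaths before 12 months as the worst outcome.
- **Text:** state which patients enter the primary analysis and how deaths are treated in it.

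Cost: slightly more analysis work and no new visits or data. The model assumes data missing at random given the observed volumes, and it does not recover patients lost before the 3-month echo. The delta-adjusted and death-ranked analyses are needed for those two reasons.
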